## Abstract

**Introduction:**

Pain is an expected and appropriate experience following traumatic musculoskeletal injury. By contrast, chronic pain and disability are unhelpful yet common sequelae of trauma-related injuries. Presently, the mechanisms that underlie the transition from acute to chronic disabling post-traumatic pain are not fully understood. Such knowledge would facilitate the development and implementation of precision rehabilitation approaches that match interventions to projected risk of recovery, with the aim of preventing poor long-term outcomes. The aim of this study is to identify a set of predictive factors to identify patients at risk of developing ongoing post-traumatic pain and disability following acute musculoskeletal trauma. To achieve this, we will use a unique and comprehensive combination of patient-reported outcome measures, psychophysical testing and biomarkers.

**Methods and analysis:**

A prospective observational study will recruit two temporally staggered cohorts (n=250 each cohort; at least 10 cases per candidate predictor) of consecutive patients with acute musculoskeletal trauma aged ≥16 years, who are emergency admissions into a Major Trauma Centre in the United Kingdom, with an episode inception defined as the traumatic event. The first cohort will identify candidate predictors to develop a screening tool to predict development of chronic and disabling pain, and the second will allow evaluation of the predictive performance of the tool (validation). The outcome being predicted is an individual’s absolute risk of poor outcome measured at a 6-month follow-up using the Chronic Pain Grade Scale (poor outcome ≥grade II). Candidate predictors encompass the four primary mechanisms of pain: *nociceptive* (eg, injury location), *neuropathic* (eg, painDETECT), *inflammatory* (biomarkers) and *nociplastic* (eg, quantitative sensory testing). Concurrently, patient-reported outcome measures will assess general health and psychosocial factors (eg, pain self-efficacy). Risk of poor outcome will be calculated using multiple variable regression analysis.

**Ethics and dissemination:**

Approved by the NHS Research Ethics Committee (17/WA/0421).

Strengths and limitations of this studyA comprehensive array of candidate predictive factors will allow for the prediction of chronic and disabling pain following trauma.These predictive factors will enable the development and validation of a predictive tool to predict good and poor outcome at 6 months postinjury.The prospective design of the study enables control of unwarranted influences and enables a stronger case for inferring causal relationships.Identifying predictive factors related to poor outcome of pain and disability outcome will facilitate targeting of effective interventions.Other candidate predictors may have been useful to include (eg, vibration thresholds), but consideration of burden to participants of testing and sample size considerations necessitated prioritisation of candidate predictive factors.

## Introduction

Pain is an expected and appropriate experience that usually follows traumatic injury.^1^ By contrast, chronic pain and disability are unhelpful but common sequelae of trauma-related injuries.^2^ Gaining an understanding of why some people develop chronic and disabling post-traumatic pain is therefore a priority for individual patients, the military and society at large. Notwithstanding, the mechanisms that underlie the transition from acute to chronic disabling post-traumatic pain are not fully understood. Such knowledge would facilitate the development and implementation of a clinical pathway of care that matches interventions to projected risk of poor recovery, with the aim of preventing poor long-term outcomes. This project stems from advances in knowledge relating to the assessment and management of pain^3^ and the quantification of potential predictive factors to inform personalised rehabilitation; identifying which patients to target with rehabilitation and when and how to target them.

Few studies have specifically explored predictive factors for recovery, whether poor or good, following physical trauma. Of those that have psychosocial variables, such as anxiety, depression and post-traumatic stress, have so far been identified as the strongest predictors of outcome.^4–7^ However, only a limited number of variables have hitherto been evaluated as potential predictive factors. Indeed, current opinion regarding pain mechanisms^8^ suggests that the development of chronic pain and disability cannot be entirely attributable to psychosocial factors. This is consistent with research in primary care that has identified predictive factors for poor outcome across a range of musculoskeletal pain conditions,^9^ which include: widespread pain, high functional disability, high pain intensity, long pain duration, high depression/anxiety, presence of previous pain episodes, movement restriction and poor coping strategies. Moreover, developments in the mechanistic understanding of pain^10–12^ suggest that other measures (eg, indicators of central sensitisation and inflammatory activity) may have potential predictive utility, especially in an acute trauma population.

### Aims of study

Using a unique combination of (1) general patient characteristics including premorbid neuropsychological status, (2) quality of life and physical functioning, (3) psychosocial features, (4) injury characteristics, (5) pain characteristics, (6) quantitative sensory testing and (7) biomarkers, we aim to find a set of predictive factors to identify patients at risk of developing ongoing post-traumatic pain and disability following acute musculoskeletal trauma. This will subsequently inform the feasibility of developing and evaluating a new clinical care pathway of precision rehabilitation that matches interventions to the predicted risk of poor recovery.

### Objectives

(1) Identify predictive factors for poor outcome (chronic pain and disability at 6 months postinjury) following acute musculoskeletal trauma. (2) Develop a predictive model to inform a screening tool to identify the predicted risk of poor recovery (transition from acute post-traumatic pain to chronic pain and disability). (3) Estimate the predictive performance of the screening tool through validation of the model in a separate dataset. (4) Document the clinical course of symptoms at 3 and 12 months following acute musculoskeletal trauma.

## Methods and analysis

### Source of data

The study will be a prospective, observational study of two temporally staggered cohorts of patients with trauma, who are emergency department admissions into a Major Trauma Centre in the United Kingdom, with an episode inception defined as the traumatic event (figure 1). The first cohort will facilitate development of the prediction model to inform the screening tool, and the second will enable validation of the prediction model through evaluation of the predictive performance of the model and tool.^13 14^ There will be an interval of at least 6 months between recruitment into the two respective cohorts. The prospective design enables control of unwarranted influences and enables a stronger case for inferring causal relationships. The nature of the study necessitates predictive statistical modelling.^15^ This protocol is written in line with the TRIPOD (transparent reporting of a multivariable prediction model for individual prognosis or diagnosis) statement,^16^ in which recommendations are given for the reporting of prediction model development and validation.

**Figure 1 F1:**
[figure not shown]
Study design. CNS, central nervous system.

Self-reported and physical assessment predictive data will be collected at baseline over a period of up to 14 days (or duration of inpatient stay if shorter), which will commence immediately following recruitment. Biomarker data collection will occur throughout the same baseline period, but can commence prior to recruitment providing assent is gained from a legal consultee. The outcome data will be collected at 6 months postinjury (working definition of chronic pain)^17^, the point of evaluation of an individual’s absolute risk of poor outcome (objectives 1, 2 and 3). In addition, selected data will be measured at 3 and 12 months postinjury to explore the clinical course of recovery following injury in the shorter and longer terms (objective 4).

### Participants

Participants will be recruited from the register of a Major Trauma Centre in the United Kingdom for a period of up to 24 months (planned start date January 2018). All consecutive eligible patients will be approached for recruitment until the sample size is achieved.

### Eligibility criteria

Inclusion criteria: adult patients aged ≥16 years who are admitted to emergency department of the Major Trauma Centre, with their main criteria for admission being acute musculoskeletal trauma within the preceding 14 days, and a capacity to use and understand written and verbal English language and a mental capacity to provide informed consent (eg, no confusion, delirium, severe cognitive impairment or severe mental illness, defined by a score of ≤6 on the Abbreviated Mental Test).^18^ The primary reason for including patients with trauma occurring up to 14 days, is to be inclusive of patients who are critically ill and/or with diminished mental capacity initially following their trauma, patients requiring surgery as a result of the trauma and representative of the broad trauma population.

Exclusion criteria: exclusions will be made where the patient has an acute intracranial lesion (eg, bleed) combined with a score of ≤14 on the Glasgow Coma Scale^19^ (a 15-item measure of consciousness impairment with adequate reliability^20^ that is routinely taken in patients with trauma at hospital admission), where there is evident brain or central nervous system injury or impairment, long-term neurocognitive disorders (such as brain tumour, multiple sclerosis, Alzheimer’s and Parkinson’s diseases and so on), comorbid cancer, the presence of an ongoing rheumatological condition, prolonged use of corticosteroids or terminal illness with short life expectancy.

Withdrawals: participants will be informed that they are free to withdraw from the study at any time, without needing to provide reason. In the event of death within 3 months of being recruited, participants will be automatically withdrawn from the study and the primary predictive analysis. Baseline data of all withdrawn participants will be kept and compared with those of retained participants to assess for any differences.

### Recruitment

Based on feasibility data (site data from the Trauma Audit and Research Network), it is estimated that at least 1000 eligible patients with trauma will be approachable for recruitment over a 24-month period, and that 50% would be expected to consent to participation. A dedicated team of research nurses will be available to recruit patients 7 days per week (from 0700 to 1930).

Because of impairments resulting from their injuries, some otherwise eligible patients will lack the mental capacity to provide informed consent when first approached to enrol in the study. Recruitment into the study will therefore be undertaken under the guidance and provision of the (UK) Mental Capacity Act 2005 for research in emergency situations. If the patient lacks sufficient capacity to consent, written assent for study participation will be sought from a legal consultee to begin biomarker data collection (blood samples), with informed consent for full recruitment (and subsequent data collection) being sought from the patient only if, and when, they regain sufficient capacity to provide this. If the patient does not regain capacity to provide consent within 14 days of their trauma, they will not be recruited into the study, biomarker data collection will cease and any blood samples already collected will be destroyed before analysis.

Once informed consent is gained and the participant recruited, following a minimum 1 hour lead time after the informed consent process (to reduce patient burden), members of the research team will visit the patient at their bedside to collect baseline self-reported data via questionnaires (table 1). On the next available working day following completion of the questionnaires (again, to reduce patient burden), members of the study team will return to the patient to conduct the first physical (quantitative sensory testing) assessment. At each visit, if deemed necessary, the capacity of the participant will be checked using an Abbreviated Mental Test^18^ (a score of ≤6 is indicative of reduced capacity), and asked if they are happy to proceed with data collection.

**Table 1 T1:** Summary of data collection at different assessment points

Domain/Candidate predictor	Measure/data item	Baseline *commencing ≤14 days post-trauma*	3-month *clinical course*	6-month *outcome assessment point/clinical course*	12-month *clinical course*
General patient characteristics including premorbid neuropsychological status					
Age	In years	√			
Gender	Female/male/other	√			
BMI	Calculated from height and weight measurements	√			
Education	Highest educational level attained	√			
Employment status	Full time/part time/not working/retired/student Employed/self-employed	√	√	√	√
Circumstance of trauma	Military/civilian	√			
Previous history of musculoskeletal pain and injury	Patient history data from patient recollection and medical records	√			
Comorbidity of other health problems	Patient history data from patient recollection and medical records	√			
Premorbid physical health	Patient history data from patient recollection and medical records	√			
Premorbid psychological health	Patient history data from medical records and patient recollection (including non-somatic items from the Subjective Health Complaints Inventory)^44^	√			
Number of days in hospital	Intensive care/ward/total	√			
Quality of life and physical functioning					
General health	SF-36v2^45^	√	√	√	√
Health-related quality of life	EuroQol EQ-5D-5L^46^	√	√	√	√
Self-care and mobility during activities of daily living	Barthel Index of Activities of Daily Living,^47^ collected from hospital data	√			
Sleep quality	11-point (0–10) Numerical Rating Scale, relating to current pain, from ‘best possible sleep’ to ‘worst possible sleep’^48^	√	√	√	√
Brain/CNS impairment	Glasgow Coma Scale^19^	√			
Psychosocial features					
Anxiety and depression	HADS^49^	√	√	√	√
Coping strategies applied during a painful experience	CSQ-24^50^	√	√	√	√
Fear of movement or fear of injury or re-injury during movement	TSK-11^51^	√	√	√	√
Confidence in ability to perform activities despite pain	Pain Self-Efficacy Questionnaire^52^	√	√	√	√
Subjective post-traumatic distress	IES-R^53^	√	√	√	√
Injury characteristics					
Time of injury/incident	Hospital record data	√			
Injury location	Adapted pain drawings, based on hospital record data	√			
Tissues damaged	Based on imaging data and hospital records Fractures Penetrating/non-penetrating injury/both	√			
Surgery required	Location and postinjury timing of surgery, based on hospital record data	√			
Assisted mechanical ventilation required	Yes/no/duration	√			
Severity of injury	Injury Severity Scale^54^	√			
Pain characteristics					
Chronic pain severity	Chronic Pain Grade Scale^21^			√	√
Pain intensity	11-point (0–10) Numerical Rating Scale, relating to current pain, from ‘no pain’ to ‘pain as bad as could be’ (collected as part of the Chronic Pain Grade Scale)	√*	√	√	√
Pain medication intake (type, dosage and timing)	Medication Quantification Scale,^55–57^ based on hospital record data	√*			
Pain location	Pain drawing	√*	√	√	√
Pain extent	Electronic pain drawing^58^	√*			
Self-reported features of neuropathic pain	painDETECT questionnaire^59^	√*	√	√	√
Quantitative sensory testing					
Heat pain threshold	Evaluation of pain threshold using a heat stimulus	√*			
Cold pain threshold	Evaluation of pain threshold using a cold stimulus	√*			
Pressure pain threshold	Evaluation of pain threshold using a pressure stimulus	√*			
Temporal summation	Evaluation of pain intensity in response to repetitive pressure stimuli	√*			
Biomarkers					
CRP	Serum levels of CRP, a broad indicator of inflammation (via blood analysis)	√†			
cfDNA	Plasma levels of cfDNA (nuclear and mitochondrial), indicators of tissue damage (via blood analysis)	√†			

*Measurements to be taken repeatedly throughout the baseline period, which will commence immediately following recruitment via informed consent (up to 14 days post-trauma) for a period of up to 14 days (i.e. until a maximum of 28 days post-trauma), while the participant is in hospital.

†Measurements to be taken repeatedly throughout the baseline period, but may be commenced prior to this, subject to assent from a legal consultee.

BMI, body mass index; cfDNA, cell-free DNA; CRP, C reactive protein; CSQ-24, Coping Strategies Questionnaire-2; HADS, Hospital Anxiety and Depression Scale; IES-R, Impact of Event Scale revise; SF-36v2, 36-item Short Form Health Survey, version 2; TSK-11, Tampa Scale of Kinesiophobia, 11-item.

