### Sample size

In predictive modelling, a larger sample size enables lower bias and variance, and permits the prospective prediction of new observations.^15^ The number of predictors will be reduced using exploratory factor analysis. This process will ensure that the sample size provides at least 10 cases per candidate predictor, to adequately power the final regression analysis.^35 36^ Data will be collected for an estimated 300 participants per cohort (n=600 total) to allow for withdrawals (primarily expected deaths within the first 3 months) and losses to follow-up, so that final data are available for 250 participants per cohort (n=500 total).

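### The stated recruitment inputs yield 500 participants at the planning minimum, not the 600 the sample size requires, and the shortfall would fall on the validation cohort

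*Protocol article*

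**What the plan says.** All of the following is in the protocol article.

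- **Recruitment:** the estimate is that "at least 1000 eligible patients with trauma will be approachable for recruitment over a 24-month period, and that 50% would be expected to consent".
- **Sample size:** "Data will be collected for an estimated 300 participants per cohort (n=600 total) to allow for withdrawals" and losses to follow-up. The same sentence sets the number with final data at 250 per cohort, 500 in total.
- **Participants:** patients are recruited from the centre's register "for a period of up to 24 months (planned start date January 2018"). Every consecutive eligible patient is approached until the sample size is reached.
- **Source of data:** "There will be an interval of at least 6 months between recruitment into the two respective cohorts". The first cohort develops the model and the second validates it.
- **Statistical analysis methods:** in the first cohort the candidate predictors are cut to 25, on the ground that a cohort of 250 supports that number.
- **Abstract, Methods and analysis:** the study "will recruit two temporally staggered cohorts (n=250 each cohort"), so 250 is given as the number recruited.

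**The concern.** The feasibility estimate and the recruitment period cover the same 24 months, so the estimate should yield the number to be recruited. It yields the number to be analysed instead. No section explains how the extra 100 participants are found.

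The interval between cohorts may make this worse. One start date and one period of up to 24 months are given, and at least 6 months must separate recruitment into the two cohorts. If no one is recruited during that time and it counts towards the 24 months, the active period is shorter than the one the feasibility estimate assumes.

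At stake is Objective 3, the estimate of the tool's predictive performance in separate data. The validation cohort is recruited last, so a fixed end date cuts it first.

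**Working it through.** **Inputs.** Approachable patients: 1000 per 24 months, taken at the stated minimum. Consent: 50%. Required: 300 recruited and 250 analysed per cohort. Window: 24 months. Interval: at least 6 months. Accrual is assumed constant.

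**1. The sample-size chain.** 25 predictors x 10 = 250 per cohort; x 2 = 500 with final data. Recruited: 300 x 2 = 600. The implied loss is 1 - 250/300 = 16.7%, or 1 in 6; no loss rate is stated. This chain is internally consistent.

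**2. The recruitment yield.** 1000 x 0.50 = 500. Against 600, the shortfall is 100, and 100/600 = 16.7%.

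**3. What would close the gap.** Approachable patients needed: 600/0.50 = 1200. Or consent needed: 600/1000 = 60%. Or active time needed: the rate is 500/24 = 20.8 consents a month, and 600/20.83 = 28.8 months.

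**4. If 6 recruitment-free months lie inside the 24.** Active time: 24 - 6 = 18 months. Yield: 500 x 18/24 = 375. The interval is a minimum, so 375 is the most this reading gives at 1000 approachable. Reaching 600 in 18 months would need 600/750 = 80% consent.

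**5. Where the shortfall falls.** Cohort 1 reaches 300 in 300/20.83 = 14.4 months, which gives 250 analysable at the implied loss. Cohort 2 has what remains:

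| | Months left | Recruited | Analysable (x 250/300) |
|---|---|---|---|
| Plan | – | 300 | 250 |
| No gap inside the window | 24 - 14.4 = 9.6 | 9.6 x 20.83 = 200 | about 167 |
| 6-month gap inside the window | 24 - 14.4 - 6 = 3.6 | 3.6 x 20.83 = 75 | about 62 |

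**6. Effect on precision.** Standard errors scale roughly with 1/√n at the same outcome proportion. Against 250 analysable, intervals for the performance measures widen by √(250/166.7) = 1.22 without a gap, and by √(250/62.5) = 2.0 with one.

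**The case against.** The strongest reply is that 1000 is a floor. The text says at least 1000, and 1200 approachable patients at 50% consent would give 600. This stands against any claim that the target is out of reach, which a reader might infer. It does not reconcile the figures: 1000 is the only planning number given, and the article does not say that 1200 are expected.

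A second reply is that recruitment continues until the sample size is reached. The same section limits recruitment to 24 months, and it already approaches every consecutive eligible patient, so there is no further pool to draw on.

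Third, 375 could be taken as the expected yield. The documents do not support that as a flat statement. A single period with a single start date suggests that the interval lies inside the 24 months, but no section says so. If the 24 months are active recruiting time, or the interval runs from the start of one cohort to the start of the next, the yield stays at 500. No reading of the interval raises it to 600.

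Fourth, a reader might split the shortfall equally between the cohorts and conclude that 25 predictors can no longer be supported. That does not follow. The cohorts are recruited in sequence, the predictor limit concerns only the first, and the first can reach 300 well within the window.

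Finally, the abstract's 250 agrees with the number analysed, and calling it recruited may be no more than loose wording. That mismatch is minor and adds nothing to the shortfall.

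**Conclusion.** The point holds as a mismatch between stated figures. At the planning minimum the recruitment inputs support 500 recruits against 600 required, a shortfall of 100 (16.7%). This part needs only the article's own numbers, with 1000 taken as the planning figure.

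The drop to at most about 375 is conditional. It assumes constant accrual and a recruitment-free interval inside the 24 months, and the article leaves the position of the interval open.

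The development cohort, with its 250 analysable participants and 25-predictor limit, can stand. The exposed part is validation: about 200 recruited and 167 analysable without a gap, or about 75 and 62 with one. These figures assume that cohort 1 is filled to 300 first and that losses run at the implied 1 in 6. The mismatch does not itself bias any estimate. It means that the planned precision of the validation is not supported by the plan's inputs.

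**What to change.** Reconcile the abstract with the Source of data, Participants, Recruitment and Sample size sections.

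1. State whether the interval of at least 6 months lies inside or outside the 24 months, whether recruitment stops during it, and whether it runs from the end or the start of cohort 1 recruitment.
2. Then choose one of two courses:
   - Restate the calendar: about 28.8 months of active recruitment at the stated rates, plus the interval if it is recruitment-free (28.8 + 6 = 34.8, about 35 months at the minimum interval).
   - Keep 24 months and restate the expected recruited and analysable numbers, above all for the validation cohort, with the precision they give for its performance estimates.
3. If more than 1000 approachable patients or more than 50% consent is expected, state the figure and its basis.
4. As a minor correction, give 300 recruited and 250 analysed per cohort in the abstract.

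The cost is a longer stated timeline or a less favourable stated validation sample. No study procedure changes.
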